#### 7.1.6.2.2 Diameter measurement method:

Maintain the postoperative annular shape, measure the average of three diastolic annular diameters using TTE or TEE.

- Annular long diameter (A2): Measured in the standard apical four-chamber view, representing the left-right diameter of the tricuspid annulus.
- Annular short diameter (B2): Measured in the standard right ventricular inflow view, representing the superior-inferior diameter of the tricuspid annulus.

[figure not shown]

An increase in diameter is defined as the difference between the 180-day postoperative annular diameter and the 3-month follow-up diameter, divided by the 3-month follow-up diameter. An increase of more than 15% in both long and short diameters is considered significant.

**7.1.6.2.3 Echocardiographic parameters:** Measure right atrial and ventricular size, width of the narrowest regurgitation jet, and reverse flow area.

TTE evaluations will be conducted at discharge or 30 days ( $\pm 7$  days), 3 months ( $\pm 15$  days), 6 months ( $\pm 30$  days), and 12 months ( $\pm 30$  days) postoperatively.

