components. Anatomical studies have shown that the enlargement of the tricuspid annulus is unequal among the three leaflets, with significant posterior valve involvement, which can enlarge by about 80% compared with normal, the anterior annulus is smaller, which can enlarge by about 40% compared with normal, and the septal annulus is only enlarged by 10% ; based on these characteristics, the measurement of the tricuspid annulus depends on the size of the leaflets. The malleability of the tricuspid valve is very good and can change significantly at different pressure/load volumes, and even during atrial systole, the circumference of the annulus is reduced by approximately 19% (30% area reduction) . So, in the case of severe left heart disease with left atrial pressure overload, the pressure load is inversely transmitted, causing increased pulmonary venous pressure and pulmonary circulation congestion. Long-term pulmonary congestion leads to fibrosis of the pulmonary interstitial tissue and pulmonary vasculature, which in turn causes chronic pulmonary vascular remodeling and pulmonary artery constriction. This results in pulmonary hypertension and the formation of right ventricular pressure overload. These changes then cause dilation of the tricuspid valve, flattening and rounding of the tricuspid annulus, and alteration of the spatial relationships among the leaflets, annulus, chordae tendineae, papillary muscles, and other important tissue structures. This leads to deviation of the traction forces acting on the leaflets and asymmetric contraction of the annulus, ultimately preventing normal coaptation of the tricuspid leaflets and resulting in tricuspid regurgitation.

The 2008 ACC/AHA guidelines for valvular heart disease state  that patients with severe tricuspid regurgitation should undergo concomitant tricuspid valvuloplasty (recommendation level I) during mitral valve surgery; while for patients with mild to moderate tricuspid regurgitation, pulmonary hypertension or tricuspid annular dilatation are also recommended to perform mitral valve surgery

Stage management of tricuspid valve (but recommended grade II b). Valvular heart disease guidelines issued by the ESC/EACTS in 2012 were significantly more aggressive in recommendation levels. Simultaneous treatment of the tricuspid valve (II a) is recommended during left-heart valve

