#### **7.1.2.3 Rationale for Selecting the Primary Endpoint:**

The primary goal of the Annuloplasty Ring is to repair and reshape the diseased valve annulus, ensuring proper leaflet coaptation (the area where the valve leaflets meet). For patients with tricuspid regurgitation (leaky valve), the main evaluation metric after annulus repair is the success rate of the Annuloplasty Ring at 6 months post-surgery. Definition of Repair Success: No Severe Regurgitation: Postoperative echocardiography (heart ultrasound) must show no severe valve leakage. Annular Dilation  $\leq 15\%$ : The increase in the annular size (measured by echocardiography) must be 15% or less compared to preoperative measurements.

Secondary Efficacy Endpoints

The secondary endpoints for evaluating effectiveness include the following assessments at discharge or 30 days post-surgery (whichever comes first), and at 3 months, 6 months, and 12 months post-surgery:

Degree of Valve Regurgitation: Assessed by echocardiography (heart ultrasound) to measure the severity of valve leakage.

Echocardiographic Parameters: Changes in the following measurements will be evaluated:

Size of the right atrium and right ventricle.

Annular dimensions (diameter).

Width of the narrowest part of the regurgitant jet.

Area of reverse blood flow.

NYHA Functional Class: A measure of heart failure symptoms and functional capacity, classified as Class I (no symptoms) to Class IV (severe symptoms).

Freedom from Reoperation: The rate of patients who do not require repeat surgery for tricuspid regurgitation.

Device Performance Evaluation:

Suture Needle Ease of Use: How smoothly the needle passes through the Annuloplasty Ring during implantation.

Holder Device Usability: How user-friendly the ring holder is during the procedure.

Surgical Technical Success:

Defined as the following criteria being met before leaving the operating room:

No intraoperative death.

Successful implantation of the Annuloplasty Ring.

Successful removal of the ring holder.

No need for emergency surgery or additional interventions related to the investigational device.

Safety Endpoints:

Safety will be assessed at discharge or 30 days post-surgery (whichever comes first), and at 3 months, 6 months, and 12 months post-surgery. The following will be evaluated:

Serious Adverse Events (SAEs): Including:

Cardiovascular-related deaths linked to the device.

Major bleeding linked to the device.

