### 7.1.6.2 Methods and Timing for Evaluating, Recording, and Analyzing Efficacy Parameters

**7.1.6.2.1** Valve annuloplasty repair success is defined as no severe regurgitation and an increase in diameter  $\leq 15\%$  (based on a comprehensive assessment of regurgitation severity and diameter increase).

Tricuspid Regurgitation Assessment Index Table

| Parameter                   | None                                     | Trace                                                        | Mild               | Moderate                                            | Severe                 |
|-----------------------------|------------------------------------------|--------------------------------------------------------------|--------------------|-----------------------------------------------------|------------------------|
| Regurgitation Jet           | No regurgitation jet in the right atrium | Regurgitation jet extends $\leq 1$ cm from the valve orifice |                    |                                                     |                        |
| Absolute Regurgitation Area |                                          |                                                              | $< 5 \text{ cm}^2$ | $5 \text{ cm}^2 \leq \text{area} < 10 \text{ cm}^2$ | $\geq 10 \text{ cm}^2$ |
| Regurgitation Area Fraction |                                          |                                                              | $< 20\%$           | $20\% \sim 33\%$                                    | $\geq 33\%$            |

Absolute regurgitation area: Measured by TTE or TEE in the standard view with the most regurgitation.

Regurgitation area fraction: Measured by TTE in the apical four-chamber view or TEE in the mid-esophageal four-chamber view, or in the standard view with the most regurgitation.

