### **7.1.8 Trial Endpoints**

Primary endpoint: The success rate of valve annuloplasty repair at 6 months postoperatively, defined as no severe regurgitation and an increase in diameter  $\leq 15\%$  (based on a comprehensive assessment of regurgitation severity and diameter increase).

Secondary endpoints:

**7.1.8.1** At discharge or 30 days postoperatively (whichever comes first), 3 months, 6 months, and 12 months:

**7.1.8.1.1** Degree of valve regurgitation assessed by echocardiography (evaluated according to the tricuspid regurgitation assessment index table).

**7.1.8.1.2** Changes in echocardiographic parameters (right atrial and ventricular size, diameter, width of the narrowest regurgitation jet, and reverse flow area).

**7.1.8.1.3** NYHA functional class.

**7.1.8.1.4** Freedom from reoperation due to tricuspid valve insufficiency.

**7.1.8.2** Evaluation of the trial device's performance, including needle insertion smoothness and user-friendliness of the ring holder.

**7.1.8.3** Technical success rate of the surgery (before leaving the operating room), defined as no intraoperative death, successful implantation of the annuloplasty ring, successful removal of the ring holder, and no emergency surgery or secondary intervention related to the trial device.

**7.1.8.4** At discharge or 30 days postoperatively (whichever comes first), 3 months, 6 months, and 12 months:

**7.1.8.4.1** Incidence of serious adverse events, including cardiovascular death, major bleeding, severe damage to cardiac or other body structures, infective endocarditis, and thromboembolic events related to the trial device.

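### The both-axes rule for annular growth does not match the primary endpoint wording and is not ordered by enlargement; one axis rule is needed

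*Protocol*

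**What the plan says.** Protocol section 7.1.8 gives the primary endpoint as repair success at 6 months, "defined as no severe regurgitation and an increase in diameter" of at most 15%. The same singular wording stands in the synopsis and in sections 7.1.6.1 and 7.1.6.2.1. None of these places says which diameter is meant.

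Section 7.1.6.2.2 defines two diameters. The long diameter, A2, is "Measured in the standard apical four-chamber view, representing the left-right diameter of the tricuspid annulus". The short diameter, B2, is "Measured in the standard right ventricular inflow view, representing the superior-inferior diameter of the tricuspid annulus". The section then gives the only axis-level rule in the protocol: "An increase of more than 15% in both long and short diameters is considered significant".

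The reference time is also stated in two ways. Section 7.1.6.2.2 says: "An increase in diameter is defined as the difference between the 180-day postoperative annular diameter and the 3-month follow-up diameter", divided by the 3-month value. Section 7.1.2.3 says that the increase in annular size "must be 15% or less compared to preoperative measurements".

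**The concern.** Success or failure at 6 months is the variable on which non-inferiority is decided (sections 8.1.5 and 8.5). Take a patient without severe regurgitation whose diameters change by +40% and +14%. On the plain endpoint wording a diameter has grown by more than 15% and the patient fails. On section 7.1.6.2.2 the growth is not significant and the patient succeeds. The same measurements support two outcomes.

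The literal both-axes rule also makes enlargement failures rarer than a rule that counts either axis. In a non-inferiority trial with an expected success rate of 95% and a margin of -10 points, a component that seldom registers one-axis growth can conceal a ring that holds its shape less well in one direction. Section 6.1 lists preventing further annular expansion among the indications, so this component bears on what the device is for.

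**Working it through.** **1. The plan's own figure.** Inputs from section 8.2.1: success 95% in both arms, margin 10 points, one-sided alpha 0.025, power 80%, 1:1 allocation.

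n per arm = (1.960 + 0.842)² × 2 × 0.95 × 0.05 / 0.10² = 7.85 × 0.095 / 0.01 = 74.6, so 75.

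This reproduces the stated 75. The sample size calculation itself is not in dispute.

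**2. Is the rule ordered by enlargement?** The product A2 × B2 is proportional to the area of an ellipse with those axes.

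| Change in the two axes | Product | Both above 15%? |
|---|---|---|
| +50% / 0% | 1.50 × 1.00 = 1.50 (+50%) | No, passes |
| +40% / +14% | 1.40 × 1.14 = 1.60 (+60%) | No, passes |
| +40% / +10% | 1.40 × 1.10 = 1.54 (+54%) | No, passes |
| +16% / +16% | 1.16 × 1.16 = 1.35 (+35%) | Yes, fails |

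The first three patients have the larger enlargement and pass; the last has the smallest and fails. This needs no assumption about rates or measurement error. A pass here still requires that severe regurgitation is absent.

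**3. How far apart are the two readings?** The document gives no measurement error, so the SD is assumed. Take a stable annulus, the same SD for each recorded value, normal errors, and a correlation of 0 to 0.5 between the changes in the two axes. The SD of a change is SD × √2. Let q = P(change > 15%) in one axis. With zero correlation, both = q² and either = 2q − q². With correlation, both comes from the bivariate normal and either = 2q − both.

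| Assumed SD | SD of change | q | Both | Either | Gap (points) |
|---|---|---|---|---|---|
| 5% | 7.1% | 1.7% | 0.03–0.3% | 3.1–3.4% | about 3 |
| 8% | 11.3% | 9.2% | 0.9–2.9% | 15.6–17.6% | 13–17 |
| 10% | 14.1% | 14.4% | 2.1–5.5% | 23.4–26.8% | 18–25 |

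These are differences in the level of failure, the same in each arm. They are not differences between arms.

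**4. Can a between-arm difference be hidden?** This needs further assumptions: 5% severe regurgitation in each arm, independent of growth; growth above 15% in any one axis in 15% of test and 5% of control patients; correlation 0 to 0.8 between axes; 75 evaluable per arm; Newcombe 95% interval as in section 8.1.5. The true difference in success is 0.95 × (control enlargement failures − test enlargement failures).

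- Both axes, correlation 0: 0.95 × (0.0025 − 0.0225) = −1.9 points. Correlation 0.8: −6.3 points.
- Either axis, correlation 0: 0.95 × (0.0975 − 0.2775) = −17.1 points. Correlation 0.8: −12.7 points.

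The chance of declaring non-inferiority is 11% to 48% under the both-axes rule and at most 1% under the either-axis rule. This shows the mechanism; it is not an estimate for these rings.

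**The case against.** The protocol says that growth in both diameters is significant. It does not say that failure occurs only then; the link to failure comes from the shared 15% threshold. The text reads as a translation, and the word rendered as both may have meant each or either. This stands, and for that reason the point is a conflict between sections that must be reconciled, not proof that the trial will pass one-axis growth.

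Three stronger inferences are tempting, and the document supports none of them.

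- *One-axis growth is the expected pattern.* Section 4.2 describes unequal enlargement, "with significant posterior valve involvement, which can enlarge by about 80% compared with normal", about 40% anterior and 10% septal. Those figures concern leaflet segments of the diseased native annulus. They are not changes in A2 or B2 after a ring is implanted, so they do not predict the pattern of postoperative growth.
- *The choice of rule shifts the result by more than the 10-point margin.* The margin applies to test minus control. The noise model in step 3 moves both arms equally, and at a 5% SD the gap is only about 3 points. Section 7.1.6.2.2 also averages three measurements. If 8% were the SD of a single reading with independent errors, the averaged SD would be 8/√3 = 4.6% and either-axis failures about 2%. Between-visit error does not average out fully, so that is a lower bound.
- *Taking the mean of A2 and B2 solves the problem.* With equal diameters, +30% in one axis and none in the other gives a mean rise of exactly 15%, detected half the time. If the shorter of two diameters of 40 and 30 mm (assumed) spreads by 30%, the mean rises (40 + 39)/70 − 1 = 12.9%, detected about 40% of the time at an 8% SD. For comparison, the both-axes rule detects the +30% / 0% case 8% to 9% of the time at that SD. The mean is better, but not complete.

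**Conclusion.** The point holds as a contradiction within the protocol and as a defect in the rule as written. The endpoint wording and section 7.1.6.2.2 can classify the same patient differently. Followed literally, the both-axes rule passes larger enlargements than some that it fails. Neither conclusion rests on an assumption.

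The rule can also hide a one-axis difference between rings, in the direction that favours a non-inferiority claim. How much depends on per-axis growth rates and measurement error that the document does not give: the both/either gap for a stable annulus runs from about 3 points (SD 5%) to 25 points (SD 10%). These figures take each patient's change between two postoperative echocardiograms, as in section 7.1.6.2.2; they do not carry over to a preoperative reference. A reader should not infer that the trial is biased by a known amount, or that the component has no effect.

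**What to change.** Before any outcome data are analysed:

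1. Replace the both-axes sentence in section 7.1.6.2.2 with one axis rule that agrees with the endpoint and rises with enlargement. An example is a single measure built from A2 and B2, such as their product or mean, with the threshold stated on that scale. If 15% per axis is carried to the product, the threshold is 1.15² − 1 = 32%. The choice between product, mean and either-axis is partly judgement and should be justified.
2. State that rule identically in the synopsis and in sections 3.2, 7.1.2.3, 7.1.6 and 7.1.8.
3. Reconcile the reference time (3-month in section 7.1.6.2.2, preoperative in section 7.1.2.3). No axis rule can be applied until this is settled.
4. Report the either-axis and both-axes versions as sensitivity analyses.

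The cost is wording and one derived variable from measurements already taken. Slightly more failures will be counted than under the both-axes rule, so check that 95% expected success still fits. By the formula in step 1, 92% in both arms would need 116 per arm and 90% would need 142.

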#### **7.1.6.2.4 NYHA Functional Class**

| Class | Description                                                                                                                                                                                                         |
|-------|---------------------------------------------------------------------------------------------------------------------------------------------------------------------------------------------------------------------|
| I     | Patients with cardiac disease but without limitations in physical activity. Ordinary physical activity does not cause undue fatigue, palpitation, dyspnea, or angina.                                               |
| II    | Patients with cardiac disease resulting in slight limitation of physical activity. Comfortable at rest, but ordinary physical activity results in fatigue, palpitation, dyspnea, or angina.                         |
| III   | Patients with cardiac disease resulting in marked limitation of physical activity. Comfortable at rest, but less than ordinary activity causes fatigue, palpitation, dyspnea, or angina.                            |
| IV    | Patients with cardiac disease resulting in inability to carry on any physical activity without discomfort. Symptoms of heart failure are present even at rest, and discomfort increases with any physical activity. |

**7.1.6.2.5 Freedom from reoperation due to tricuspid valve insufficiency.**

**7.1.6.2.6 Technical success rate of the surgery (before leaving the operating room):**

Defined as no intraoperative death, successful implantation of the annuloplasty ring, successful removal of the ring holder, and no emergency surgery or secondary intervention related to the trial device.

### **7.1.7 Safety Evaluation Methods**

#### **7.1.7.1 Description of Safety Parameters**

Safety endpoints:

**7.1.7.1.1** At discharge or 30 days postoperatively (whichever comes first), 3 months, 6 months, and 12 months:

- Incidence of serious adverse events, including cardiovascular death, major

bleeding, severe damage to cardiac or other body structures, infective endocarditis, and thromboembolic events related to the trial device.

- All-cause mortality.
- Cardiovascular death related to the trial device.
- Major bleeding related to the trial device.
- Severe damage to cardiac or other body structures related to the trial device.
- Infective endocarditis related to the trial device.
- Thromboembolic events related to the trial device.

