| 
Statistical Methods:
 
This trial plans to enroll 164 patients, who will be randomly assigned to either the experimental group or the control group in a 1:1 ratio, with 82 cases in each group.
 
The primary endpoint of this clinical trial is the success rate of valve repair at 6 months postoperatively, defined as no severe regurgitation and an increase in annular diameter of <math>\leq 15\%</math> based on echocardiographic evaluation. According to literature reports and clinical experience, the expected success rate of valve repair in the control group at 6 months postoperatively is 95%. Assuming that the investigational medical device can achieve comparable efficacy, the clinically accepted non-inferiority margin is set at -10%. With a one-sided significance level of 0.025 and a power of 80%, the sample size was estimated using PASS 14.0 software, indicating that 75 cases are required for each group. Considering potential dropouts during the study, the plan is to enroll 82 cases per group, totaling 164 cases.
 
The trial results will be determined based on the difference in the primary efficacy endpoint between the experimental group and the control group. If the lower limit of the 95% confidence interval for the difference in success rates between the experimental group and the control group is
 |                                                                                                                                                                                                                                                                                                                                                                                                                                                                                                                                                                                                                                                                                                                                                                                                                                                              |

greater than -10% (the predefined non-inferiority margin), the non-inferiority conclusion will be established. Otherwise, the non-inferiority conclusion will not be supported.

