Biomedical Engineering Co., Ltd., while the control group will use the cardiac annuloplasty ring manufactured by Edwards Lifesciences (Shanghai) Medical Products Co., Ltd., for tricuspid valve annuloplasty. Imaging and/or clinical follow-up will be performed intraoperatively, before discharge or 30 days  $\pm$  7 days postoperatively, 3 months  $\pm$  15 days postoperatively, 6 months  $\pm$  30 days postoperatively, and 12 months  $\pm$  30 days postoperatively. The primary study endpoint is the success rate of annuloplasty ring repair at 6 months after surgery, defined as the absence of severe regurgitation and  $\leq$  15% increase in radial line value (based on a comprehensive determination of the degree of regurgitation and increase in radial line value) as evaluated by echocardiography. Secondary effectiveness evaluation endpoints include the degree of regurgitation indicated by cardiac ultrasound before discharge or at 30 days after operation (whichever comes first), and at 3, 6, and 12 months after operation, changes in echocardiographic parameters (right atrium size, right ventricular size, diameter value, width of the narrowest part of the regurgitant bundle, and reverse flow area), NYHA functional classification, and freedom from reoperation of the tricuspid valve due to tricuspid insufficiency. Performance evaluation of the test device includes smooth needle insertion and ease of use of the ring holding device and technical success rate of the operation (before leaving the operating room), defined as no intraoperative death, successful ring implantation, and holding Successful removal of the device without emergent procedure or secondary intervention related to the investigational device; Safety endpoints included the incidence of serious adverse events (such as cardiovascular death related to the investigational device, major bleeding, major damage to cardiac or other body structures, infective endocarditis, thromboembolic events), all-cause death, cardiovascular death related to the investigational device, major bleeding related to the investigational device, major damage to cardiac or other body structures related to the investigational device, infective endocarditis related to the investigational device, thromboembolic events related to the investigational device, device defects, and other adverse events occurring before discharge or within 30 days after the procedure, whichever came first. Follow-up assessments included clinical symptoms and signs, laboratory examinations, ECG, color Doppler ultrasound, and recording of adverse events, all aimed at verifying the safety and effectiveness of the investigational annuloplasty ring.

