| 5 Fatal bleeding        | 5a | Possible fatal bleeding; non-pathological or imaging basis but clinically suspicious                                                                                                                                                                                                                                                                                                                                     |
|                         | 5b | Determine the presence of fatal bleeding with obvious signs of bleeding or with pathological or imaging evidence                                                                                                                                                                                                                                                                                                         |

- Severe damage to cardiac or other body structures related to the trial device.
- Infective endocarditis related to the trial device.
- Thromboembolic events related to the trial device: Defined as myocardial

infarction, cerebral infarction, or organ embolism caused by thrombosis, with clinical or imaging evidence of arterial occlusion.

**7.1.7.2.2** Surgical details and intraoperative complications will be recorded in the electronic case report form (eCRF). Safety evaluations will be conducted at discharge/30 days, 3 months, 6 months, 12 months, and annually from 2 to 5 years postoperatively, recording all adverse events. All eCRF data will be submitted to the statistical center for clinical data analysis and evaluation.

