## **7.2.4 Clinical Evaluation at 3 Months ( $\pm 15$ Days) Postoperatively**

**7.2.4.1** NYHA functional class.

**7.2.4.2** ECG, echocardiography (TTE).

**7.2.4.3** Record adverse events.

**7.2.4.4** Record antiplatelet or anticoagulant medications.

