## Notes:

1. Laboratory test results and electrocardiogram (ECG) examinations conducted within 15 days prior to signing the informed consent form are valid as baseline assessments.
2. Ultrasound examination (either Transthoracic Echocardiography [TTE] or Transesophageal Echocardiography [TEE], choose one) as a baseline assessment should be performed by an ultrasound physician at our hospital before the surgery. Intraoperative Transesophageal Echocardiography (TEE) is recommended.

3. Laboratory tests include complete blood count (white blood cells, red blood cells, hemoglobin, platelets), blood biochemistry (creatinine, alanine aminotransferase, aspartate aminotransferase, total serum bilirubin), and coagulation function (activated partial thromboplastin time, prothrombin time, thrombin time).
4. Visit 3---Before discharge or 30±7 days post-operation, whichever comes first.
5. Pregnancy test: If the subject is a woman of childbearing age, a blood or urine pregnancy test should be performed as needed.
6. Record the use of antiplatelet or anticoagulant medications.
7. Cardiac ultrasound examinations should be performed by a qualified physician at our hospital; the same subject's ultrasound examinations should be conducted at the same center; follow-up results will be independently interpreted by a senior ultrasound physician.
8. The surgery should be performed by a designated surgeon.

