##### **8.1.6.2 Secondary Safety Endpoint Analysis**

**8.1.6.2.1** The incidence of device-related serious adverse events (SAEs) at discharge or 30 days, 3 months, 6 months, and 12 months post-surgery will be compared between groups using the chi-square test or Fisher's exact test.

**8.1.6.2.2** The incidence of all-cause mortality at discharge or 30 days, 3 months, 6 months, and 12 months post-surgery will be compared using the chi-square test or Fisher's exact test.

**8.1.6.2.3** The incidence of cardiovascular death related to the test device at discharge or 30 days, 3 months, 6 months, and 12 months post-surgery will be compared using the chi-square test or Fisher's exact test.

**8.1.6.2.4** The incidence of major bleeding related to the test device at discharge or 30 days, 3 months, 6 months, and 12 months post-surgery will be compared using the chi-square test or Fisher's exact test.

**8.1.6.2.5** The incidence of severe damage to cardiac or other body structures related to the test device at discharge or 30 days, 3 months, 6 months, and 12 months post-surgery will be compared using the chi-square test or Fisher's exact test.

**8.1.6.2.6** The incidence of device-related infective endocarditis at discharge or 30 days, 3 months, 6 months, and 12 months post-surgery will be compared using the chi-square test or Fisher's exact test.

**8.1.6.2.7** The incidence of thromboembolic events related to the test device at discharge or 30 days, 3 months, 6 months, and 12 months post-surgery will be compared using the chi-square test or Fisher's exact test.

**8.1.6.2.8** The incidence of adverse events from postoperative to 5-year follow-up will be compared using the chi-square test or Fisher's exact test.

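### The first safety and reoperation count closes at the earlier of discharge and day 30, so its length varies with hospital stay, yet the safety counts are compared as crude proportions

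*Protocol*

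**What the plan says.** Protocol 7.1.7.1 sets the time points for serious adverse events, all-cause mortality and the device-related components: "At discharge or 30 days postoperatively (whichever comes first), 3 months, 6 months, and 12 months". Section 7.1.8.4 and the synopsis give the same list, and 7.1.2.3 agrees: "Safety will be assessed at discharge or 30 days post-surgery (whichever comes first), and at 3 months, 6 months, and 12 months post-surgery". Reoperation for tricuspid insufficiency is an efficacy endpoint, but 7.1.6.1.1 and 7.1.8.1 give it the same first time point.

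Section 3.2 words the rule as a window for counting events, "occurring before discharge or within 30 days after the procedure, whichever came first", and attaches no later time point to the safety endpoints there. Note 4 to the flowchart in 7.2.8 ties the visit to the same rule: "Visit 3---Before discharge or 30±7 days post-operation, whichever comes first". The next scheduled contact is the 3-month visit, ±15 days (7.2.4).

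For the analysis, 8.1.6.2.2 states "The incidence of all-cause mortality at discharge or 30 days, 3 months, 6 months, and 12 months post-surgery will be compared" by chi-square or Fisher's exact test. The other safety endpoints with these time points are treated alike. The wording there no longer says that the earlier of the two dates applies. Section 8.1.6.1.4 names the same tests for reoperation, without time points.

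**The concern.** A cumulative incidence is interpretable when every patient is at risk of being counted over the same period. Here the period ends at discharge for anyone who leaves before day 30. Discharge happens after treatment and depends partly on how the patient fared: an uncomplicated patient leaves early and is counted for a short time, while a patient kept in with a complication is counted for longer. The window is thus linked to the outcome that it measures.

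The rate also depends on local discharge practice. The trial is to run at more than ten (7.1.2.1) and at most 20 (7.1.5.4) sites with competitive enrolment (8.2.3). At stake is the reading of the perioperative safety table: a row labelled discharge or 30 days could be taken for a 30-day rate when it is largely an in-hospital rate. If stays differed between the arms, the early rates would differ for that reason alone.

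**Working it through.** The plan gives no figure for this point. Its one computed figure, 75 per group, belongs to the 6-month efficacy endpoint and has no bearing here.

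**Window implied by the text.** For a patient with length of stay L days, the first count runs over min(L, 30) days. A patient still in hospital may have Visit 3 as late as 30 + 7 = 37 days. With 30-day months, the 3-month visit falls at 90 − 15 = day 75 at the earliest. Take a patient discharged on day 8 who has an embolus on day 15: the event lies outside the first count and is due to be picked up by the 3-month visit at the latest.

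**Inputs.** From the protocol: the 30-day limit and 82 patients per group (8.2.1). Assumed, because the protocol gives neither length of stay nor early event rates: discharge on day 7, 14 or 21; a 30-day risk r of 5% or 10%; and a hazard that is either constant (k = 1) or front-loaded (Weibull shape k = 0.5).

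**Share of 30-day events outside the first count.** For small risks this is about 1 − (L/30)^k.

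| Discharge day L | Share of 30 days covered | Outside, constant hazard | Outside, front-loaded hazard |
|---|---|---|---|
| 7 | 7/30 = 23% | 77% | 1 − √(7/30) = 52% |
| 14 | 14/30 = 47% | 53% | 1 − √(14/30) = 32% |
| 21 | 21/30 = 70% | 30% | 1 − √(21/30) = 16% |

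**In events.** Let H = −ln(1 − r). The risk by day L is 1 − exp(−H(L/30)^k). With r = 5%, 82 × 0.05 = 4.1 events per arm are expected by day 30. The first count would show:

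- constant hazard: 1.0 (day 7), 1.9 (day 14) or 2.9 (day 21);
- front-loaded hazard: 2.0, 2.8 or 3.4.

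**Effect of stay alone.** Give both arms the same constant hazard with r = 10%, so H = 0.105. If all patients stayed 7 days in one arm and 14 in the other, the first-count incidences would be 1 − exp(−0.105 × 7/30) = 2.4% and 1 − exp(−0.105 × 14/30) = 4.8%. This shows the mechanism; nothing in the protocol suggests that stays will differ between the rings.

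**The case against.** The strongest reply is that no event is lost to the trial. Adverse events are recorded at every visit, and 7.1.7.2.2 carries this on "annually from 2 to 5 years postoperatively, recording all adverse events". Section 13.1 requires all adverse events to be recorded, and 13.3 and 20.2.8 require serious ones to be reported as they occur, with a 24-hour limit for the written report to the ethics committee and authorities. A reader might infer from the missing day-30 contact that deaths, bleeds or emboli after discharge go unascertained. The documents do not support that. Only the first of four tabulations closes early, and the 3-, 6- and 12-month time points do not depend on discharge. The protocol does not say that counts are cumulative, but if they are, these events enter the 3-month figure.

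A reader might also infer that the comparison between rings is biased. Dynamic randomisation balances on centre (7.1.2.2), so differences in discharge practice between centres should fall about equally on both arms. A difference in stay caused by the device is possible but not evidenced.

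Third, no trial decision rests on this table. Success is judged on the 6-month efficacy endpoint alone (8.5), and an early count tied to discharge is a recognisable design choice. A day-30 tabulation could also be added in the SAP.

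All of this limits the point without removing it. The protocol itself fixes the variable window and the crude comparison, so the point is a stated rule that can be improved, not a detail left for the SAP.

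**Conclusion.** The point holds for one tabulation. The first safety and reoperation count has a patient-specific length that depends on the postoperative course, and the safety counts are compared as though it did not. For patients discharged before day 30 it is an in-hospital count and should not be read as a 30-day rate.

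The size cannot be derived from the protocol. The ranges of 53–77% (constant hazard) and 32–52% (front-loaded) for discharge on day 7 to 14 rest wholly on assumed stays and hazard shapes and are illustration only. At an assumed 5% risk they amount to roughly one to three events per arm. The primary endpoint, the sample size and the later safety time points are unaffected. The change is worth making because it is cheap and yields an early rate that is comparable across patients and centres.

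**What to change.** Keep Visit 3 as it is for examination, ECG and echocardiography. Define the first safety and reoperation time point as events with onset on or before postoperative day 30 in every patient. Classify events by onset date, drawing on Visit 3, SAE reports and the 3-month visit. Report in-hospital events as a separate row if wanted.

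Align every place that carries or analyses the rule: the synopsis (secondary endpoints and trial design), 3.2, 7.1.2.3, 7.1.6.1.1, 7.1.7.1.1, 7.1.8.1, 7.1.8.4, 8.1.6.1.4 and 8.1.6.2. In the same edit, bring 3.2 into line with the sections that also list 3, 6 and 12 months for safety.

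The cost is wording and a date-based derivation; check that the eCRF holds an onset date for each event. No extra visit is needed. The registration report follows the 6-month visit, by when the 3-month data are due, so there should be no delay. There are two downsides: early rates may look slightly higher, and the day-30 status of discharged patients is confirmed only at the 3-month visit.
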